#### Virological endpoints

1. Proportions of patients with a negative nasopharyngeal swab and sputum sample for SARS-CoV-2 quantitative RT-PCR on days 3, 7, 10, 14, and 21 after starting treatment

2. Viral load change (log10 viral load) of nasopharyngeal swab and sputum sample for SARS-CoV-2 quantitative RT-PCR on days 3, 7, 10, 14, and 21 after starting treatment

#### Safety outcomes

Adverse events that occurred during treatmentSerious adverse eventsPremature discontinuation of treatment

## Participant timeline {13}

Nafamostat mesylate protocol schedule of enrolment, interventions, and assessments

**Table Tabb:** 

	Screening	Allocation	Post-allocation					Follow-up	
TIMEPOINT**	***-D1***	***D0***	***D1***	***D3***	***D7***	***D10***	***D14***	***D21***	***D28***
**ENROLMENT:**									
**Eligibility screen**	X								
**Informed consent**	X								
**Allocation**		X							
**INTERVENTIONS:**									
*[Nafamostat mesylate]*									
*[Standard therapy]*									
**ASSESSMENTS:**									
*[SARS-CoV RT-PCR]*	X			X	X	X	X		
*[Chest X-ray]*	X			X	X	X	X		
*[Chest CT]*	X						X		
*[Physical examination]*	X								
*[Viral signs]*	X		X	X	X	X	X	X	X
*[Symptoms]*	X		X	X	X	X	X	X	X
*[Seven category ordinary scale]*	X		X	X	X	X	X	X	X
*[NEWS score]*	X				X		X	X	X
*[Blood test]*	X		X	X	X	X	X	X	X
*[Blood collection for research]*			X		X				
*[Adverse reaction]*			X	X	X	X	X	X	X

### Sample size {14}

The sample size was calculated based on the assumption that superiority test (nafamostat treatment is right) of the treatment effect (effect size 10%) between two treatment groups (control group vs. nafamostat-treated group) will be carried out. The superiority margin is set to 0.05 (5%) based on the assumption that the nafamostat-treated group shows higher effect (90.0%) over the control group (80.0%). Nafamostat will be concluded as effective when the nafamostat-treated group shows 5% of higher effect compared to the treatment rate of the control group (80%). A one-sided significance level of 0.05 and power of 80% with equal allocation to two arms would require 42 patients in each arm of the trial.

Basic parameters for the sample size calculation are as follows:
Significance level, alpha = 0.05 (one-sided test)Power = 70%/80%/90%The ratio of the control group and the experimental group (nafamostat treatment) patients is 1:1Cure rate of the control group: 80%The cure rate of the experimental group (nafamostat treatment): 90%Superiority margin: 5%Expected drop out proportion: 5% (control, experimental each)

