## Trial design {8}

The trial is designed as a randomized, open labeled, multicenter, two-arm with 1:1 allocation clinical trial in South Korea. This study compares the effect of nafamostat mesylate injection with standard treatment on 42 patients with COVID-19 pneumonia in the intervention group versus 42 patients with COVID-19 pneumonia with standard treatment only in the control group.

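### The sample-size inputs do not give 80% power at 42 patients per arm: power is about 16% against the stated 5-point margin and about 36% with no margin

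*Protocol article*

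**What the plan says.** Sample size {14} prints all the inputs and the result together:

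- Rates: control 80%; "The cure rate of the experimental group (nafamostat treatment): 90" per cent. The same section describes a "treatment effect (effect size 10%) between two treatment groups".
- Margin: "The superiority margin is set to 0.05 (5%)". Nafamostat is to be declared effective if it comes out 5% above the control rate.
- Error rates: alpha 0.05, one-sided. The parameter list gives power as 70%, 80% and 90%; the prose ties the result to 80%.
- Allocation 1:1, with 5% expected dropout in each arm.
- Result: "power of 80% with equal allocation to two arms would require 42 patients in each arm of the trial".

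Trial design {8} repeats the number ("42 patients with COVID-19 pneumonia in the intervention group" and the same number of controls), and the Abstract gives 84 in total. Statistical methods {20a} names Pearson's chi-square test for categorical variables and does not say whether it is one- or two-sided. The article gives no other rates, effect size or formula that could support 42.

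**The concern.** A difference between 80% and 90% is 10 points. Detecting it with 80% power normally takes well over 100 patients per arm, and a 5-point superiority margin halves the distance to the null and so quadruples the requirement. On its face, 42 per arm is far too few for the power claimed.

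What is at stake is how the result is read. If the assumed 10-point benefit is real, a trial with 36% power misses it about two times in three, and one with 16% power about five times in six. A reader who trusts the 80% figure may take a non-significant result as evidence against nafamostat when it would carry little information either way.

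**Working it through.** **Inputs** (all from Sample size {14}): pC = 0.80, pT = 0.90, margin m = 0.05, one-sided alpha 0.05 (z = 1.645), power 80% (z = 0.842), 1:1 allocation, 5% dropout.

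**Step 1. Try to reproduce 42.** Unpooled normal formula, per arm:

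n = (z_alpha + z_power)² × [pC(1−pC) + pT(1−pT)] / (pT − pC − m)²

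The variance term is 0.16 + 0.09 = 0.25. For 80% power, (1.645 + 0.842)² is about 6.183, so the numerator is about 1.546.

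- 5-point superiority margin, as written: 1.546 / 0.05² = 618.3, so 619. With dropout, 619 / 0.95 = 651.6, so 652.
- No margin: 1.546 / 0.10² = 154.6, so 155. With dropout, 155 / 0.95 = 163.2, so 164.
- Margin with the opposite sign (non-inferiority style, distance 15 points): 1.546 / 0.15² = 68.7, so 69. With dropout, 73.

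Evaluable patients per arm at each listed power:

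| Power | 5-point margin | No margin | Opposite-sign margin |
|---|---|---|---|
| 70% | 471 | 118 | 53 |
| 80% | 619 | 155 | 69 |
| 90% | 857 | 215 | 96 |

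The smallest entry is 53 (56 with dropout). With no margin, 80% power and one-sided 0.05, other formulas do not help: pooled variance gives 157, the arcsine formula about 154, and a continuity correction 177. The figure of 42 is not reproduced.

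**Step 2. Power at the planned size.**

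Power = Φ[(0.10 − m) / √(0.25/n) − 1.645]

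- n = 42, standard error √(0.25/42) = 0.0772. With the margin: Φ(0.648 − 1.645) = 15.9%. Without: Φ(1.296 − 1.645) = 36.4%.
- n = 40 (42 × 0.95 = 39.9), standard error 0.0791. With the margin: Φ(0.632 − 1.645) = 15.6%. Without: Φ(1.265 − 1.645) = 35.2%.

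**Step 3. Exact check by binomial enumeration at 42 per arm.** Wald test against the 5-point margin: 15.6%. One-sided Pearson test with no margin: 36.1%. Two-sided Pearson test at 0.05: about 26%. The normal approximation is adequate here.

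**Step 4. What 42 per arm can do.**

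- With no margin, 97% versus 80% gives Φ[0.17 / √((0.16 + 0.0291)/n) − 1.645], which is about 81% at n = 42 and about 80% at n = 40. Exact power is somewhat higher, 83% to 85%.
- The 95% confidence interval half-width for the difference at 80% and 90% is 1.96 × 0.0772 = 0.151, or about 15 points.

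**The case against.** **The success rule could be a bare observed difference.** If nafamostat succeeds whenever the observed difference is at least 5 points, the chance of success at 90% versus 80% is about 70% with 42 per arm and 79% with 40, close to the stated power. But when both rates are 80%, the same rule succeeds about 25% of the time (34% with 40 per arm). That contradicts the one-sided 0.05 in the same section, so this reading does not rescue the claim.

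**This is a phase 2 trial in a pandemic, reported in a condensed article.** A small phase 2 trial is legitimate, and nothing here says that 84 patients is the wrong number to recruit. The objection does not reach the power claim, because inputs and output are printed side by side and nothing needed for the check has been left to another document.

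**Stronger readings that the documents do not support:**

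- A reader might infer that 42 must come from an unstated 20-point distance, since that gives 39 evaluable and 39 / 0.95 rounds up to 42. Other mistaken routes end at 84 in total. Omitting the factor 2 gives (1.645 + 0.842)² × 0.85 × 0.15 / 0.10² = 78.8, so 79, and 79 / 0.95 rounds up to 84. A one-sample test against a fixed 80% gives 82.9, so 83, or 84 as an even total. The origin of 42 cannot be recovered from the article.
- A reader might infer that with the 5-point margin 80% power is out of reach even at 100% versus 80%. The normal formula gives 78.4% at 42 per arm, but it fails when one rate is 1; exact Wald power is 87% at 42 per arm and 84% at 40.
- A reader might count the three listed powers as a further error. The prose attaches 42 to 80%, and the list may simply condense a scenario table.

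How readers would take a null result is a prediction, not something the article states. It bears on why the correction is useful, not on whether the figure is wrong.

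**Conclusion.** Wrong as written. The requirement exceeds the stated 42 by a factor of about 15 with the margin (619/42 = 14.7) and nearly 4 without it (155/42 = 3.7), before dropout. Whether the true figure is near 16% or near 36% depends on whether the 5-point margin is part of the test, and Sample size {14} says that it is. The two-sided figure of about 26% applies only if the Pearson test is run two-sided at 0.05 with no margin.

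The conclusion takes the printed rates, margin, alpha and allocation at face value and treats the endpoint as a single comparison of two proportions. It does not depend on the choice of formula: no standard variant comes near 80% at 42 per arm with these inputs.

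**What to change.** Keep 84 patients. In Sample size {14}:

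1. Delete the claim of 80% power.
2. State whether the 5-point superiority margin and the matching success rule stand. This has to be settled first, because quoting only the no-margin power while the margin remains would overstate power about twofold.
3. Replace the claim with text such as:

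> With 42 per arm (40 evaluable), one-sided 0.05 power for 90% versus 80% is about 16% against a 5-point superiority margin and about 35% against no difference. With no margin, 80% power is reached only for about 97% versus 80% (normal approximation). The 95% confidence interval half-width for the difference is about 15 points.

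4. If 42 was derived from other assumptions, state those and show the calculation instead.

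The cost is wording only, with no extra patients. The stated power becomes less favourable.

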### Recruitment {15}

Each center will screen subjects to achieve sample size; screening will continue until the target population is achieved (10 subjects/site). To meet the target sample size, the clinical research associate of each institution identified the difficulty of recruitment and resolved the problem through the entire meeting. In addition, in order to reduce the number of participants allocated to each institution, we contacted other institutions to secure more participating institutions. The enrollment period will extend over 12 months.

## Assignment of interventions: allocation

### Sequence generation {16a}

Nafamostat mesylate with standard therapy group and standard therapy only group were assigned in a 1:1 ratio by block randomization method by institution.

The randomization generation program is as follow: randomization codes are generated using SAS® (SAS Institute, Cary, NC, USA) and assigned to a test group (nafamostat administration + standard treatment) or a control group (standard treatment) according to the generated assignment order.

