## Methods: participants, interventions, and outcomes

### Study setting {9}

This study is a multicenter trial conducted at 10 hospitals in South Korea to generalize the results, and 10 hospitals are located in various cities.

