## Outcomes {12}

### Primary outcome

The primary outcome is as follows: proportion of patients with clinical improvement as defined by live discharge from hospital or a decline of 2 categories on the seven-category ordinal scale of clinical status [time frame: day 14 and day 28]

*Seven-category ordinal scale of clinical status
Not hospitalized with resumption of normal activities;Not hospitalized, but unable to resume normal activities;Hospitalization, not requiring supplemental oxygen;Hospitalization, requiring supplemental oxygen;Hospitalization, requiring nasal high-flow oxygen therapy and/or noninvasive mechanical ventilation;Hospitalization, requiring extracorporeal membrane oxygenation and/or invasive mechanical ventilation;Death.

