## Statistical methods

### Statistical methods for primary and secondary outcomes {20a}

Intention-to-treat analysis and per protocol analysis will be conducted respectively, and intention-to-treat analysis will be performed as the main analysis.The categorical variable of the evaluation index will be analyzed using Pearson’s chi-square test, and the continuous variable will be analyzed using ANOVA or Kruskal–Wallis test.The virus removal rate on day 14, one of the secondary outcomes, will be analyzed using Pearson’s chi-square test.Time to clinical improvement will be assessed on all subjects by day 28. If there is no clinical improvement or a case of death by day 28, it will be recorded as day 28, and analyzed by Kaplan–Meier plot and log-rank test.

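### Randomization is blocked within institution, but the chi-square test named for the binary primary outcome ignores institution; it is conservative and forgoes some power if improvement rates differ between hospitals

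*Protocol article*

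**What the plan says.** All references are to the protocol article.

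- **Sequence generation {16a}:** the groups "were assigned in a 1:1 ratio by block randomization method by institution". Institution is the only stratification factor named.
- **Study setting {9}:** "This study is a multicenter trial conducted at 10 hospitals in South Korea".
- **Primary outcome:** "proportion of patients with clinical improvement as defined by live discharge from hospital or a decline of 2 categories" on the seven-category scale, at day 14 and day 28. This is a binary outcome.
- **Statistical methods {20a}:** "The categorical variable of the evaluation index will be analyzed using Pearson’s chi-square test". No stratum or covariate is attached to this test, and institution is not mentioned in any analysis in the article.
- **Sample size {14}:** 42 patients per arm, expected rates of 80% and 90%, one-sided significance level 0.05.

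**The concern.** Blocking within each hospital keeps the arms close to balanced hospital by hospital, so differences between hospitals largely drop out of the arm comparison. The pooled Pearson test does not know this. Its variance still counts the spread of improvement rates between hospitals, so its standard error is too large whenever that spread is real.

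Such a spread is plausible here. Live discharge counts as improvement, discharge is a local decision, and the trial is open label. What is at stake is efficiency: a test that rejects less often than its nominal level under the null, and a gain from the stratified design that is not collected. The article does more than leave the point open. It names an unstratified test, and an analysis plan that followed it would carry the mismatch forward.

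**Working it through.** **1. The plan's own figure, for scale.** For 80% against 90%, one-sided 0.05 and 80% power, with mean rate 0.85:

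n per arm = [1.645·√(2·0.85·0.15) + 0.842·√(0.80·0.20 + 0.90·0.10)]² / 0.10² = [1.645·0.505 + 0.842·0.500]² / 0.01 ≈ 157.

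The stated 42 is not reproduced. Power at 42 per arm is Φ[(0.10·√42 − 1.645·0.505)/0.500] = Φ(−0.365) ≈ 36%. This is a separate problem, but it sets the level at which the two tests are compared below.

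**2. Direction, by formula.** Let hospital j have improvement rate p_j, with mean p. Under no treatment effect the pooled test uses variance p(1−p) per patient. This splits into the mean of p_j(1−p_j) plus Var(p_j). Blocking removes nearly all of the second part from the true variance of the comparison. The one-sided error is therefore roughly 1 − Φ(1.645·√[p(1−p) / (p(1−p) − Var(p_j))]).

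Take p = 0.80, so p(1−p) = 0.16, with hospital log-odds normally distributed and Var(p_j) found by numerical integration:

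- SD 1: Var(p_j) = 0.0214. The ratio is 0.16/0.1386, its root is 1.074, the effective cut-off is 1.767 and the error is about 3.9%.
- SD 1.5: Var(p_j) = 0.0392. The ratio is 0.16/0.1208, its root is 1.151, the effective cut-off is 1.893 and the error is about 2.9%.

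This assumes perfect balance and many hospitals. Ten hospitals with incomplete blocks should come out a little closer to 5%, and they do.

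**3. Size, by simulation.** From the article: 84 patients, 10 institutions, 1:1 blocks within institution, 80% and 90%, one-sided 0.05. Assumed, because the article gives none of them: 8 or 9 patients per hospital, blocks of 4, and normal hospital effects on the log-odds scale with the SD shown. Marginal rates are held at the stated values. There are 40,000 trials per setting. Pearson is compared with Cochran-Mantel-Haenszel (CMH) stratified by institution. Entries are percentages, and the difference is in percentage points from unrounded values.

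| Hospital SD | Error, Pearson | Error, CMH | Power, Pearson | Power, CMH | Difference in power |
|---|---|---|---|---|---|
| 0 | 5.2 | 5.1 | 36.4 | 35.7 | −0.7 |
| 0.5 | 4.9 | 5.1 | 36.4 | 36.5 | +0.1 |
| 1 | 4.2 | 5.0 | 35.7 | 38.3 | +2.6 |
| 1.5 | 3.4 | 5.1 | 35.6 | 41.9 | +6.2 |
| 2 | 2.8 | 5.3 | 35.9 | 46.0 | +10.1 |

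A separate simulation of 20,000 trials per setting gave Pearson errors of 5.0, 5.0, 4.2 and 3.5% at SD 0, 0.5, 1 and 1.5, with CMH at 5.0 to 5.3%. Power was 36% throughout for Pearson, against 35, 36, 39 and 43% for CMH.

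**4. Robustness.** With unequal hospitals (2 to 24 patients) the pattern is the same. At SD 1 the Pearson error is 4.3% and power is 35.8% against 38.2%; at SD 1.5 the error is 3.7% and power is 36.7% against 42.1%. Two-sided, the Pearson error is 5.1, 4.7, 3.9 and 3.1% at SD 0 to 1.5, and CMH stays at 4.8 to 5.1%. CMH also holds its level with 21 sites of 4 patients. That matters because the recruitment section says more institutions were sought in order to reduce the number per site.

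**The case against.** **The article is a summary, and an unseen analysis plan could stratify.** It could. But the article positively names an unstratified test beside a stratified allocation, so the mismatch is in its text and is not merely a missing detail.

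**The harm depends on a quantity the article does not give.** This stands, and it limits the point. The article says only that the "10 hospitals are located in various cities"; it does not say that discharge practice differs. SD 1 is not a small assumption. At an 80% overall rate it puts hospitals one SD either side of the centre at about 66% and 93%; SD 1.5 puts them at about 60% and 97%. At SD 0.5 or below there is nothing material to gain.

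**A reader might infer that the planned P-values and intervals are simply wrong.** The documents do not support that. They are conservative only if hospitals differ, and the error is never in the direction of a false claim of efficacy.

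**A reader might infer that the pooled test loses power as hospitals diverge.** It does not: its power stays near 36% across the range. What is forgone is the gain that a stratified test would collect.

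**A reader might want a mixed model with institution as a random effect and baseline category as a covariate.** That has not been tested here, and the expected number of non-improvers is only 42·0.20 + 42·0.10 = 12.6, about 13 across 10 hospitals. It is not recommended.

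**Conclusion.** The point holds in a conditional form. The article randomizes by institution and names a primary test that ignores institution. If hospitals differ, that test is conservative: one-sided error is about 4.2% at SD 1 and 3.4 to 3.5% at SD 1.5, against a nominal 5%. It forgoes about 3 and 6 points of power at those values. At SD 0.5 or below the effect is negligible.

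These sizes rest on assumed hospital variation, blocks of 4 and hospitals of 8 or 9 patients. Unequal hospital sizes do not change the pattern. This is a matter of efficiency and of matching analysis to design; the validity of a positive result is not in question. It is worth changing because the trade is lopsided: less than a point lost if hospitals are alike, and several gained if they are not.

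**What to change.** In Statistical methods {20a}, for the primary outcome and the other binary outcomes, replace Pearson's chi-square by the Cochran-Mantel-Haenszel test stratified by institution. Report the Mantel-Haenszel risk difference with its confidence interval. If very small sites are to be pooled, state the rule in advance.

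The cost is wording only, because institution is already recorded for randomization. The statistical downside is about 1 point of power or less if hospitals do not differ.

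The change is meant for binary outcomes only. For time to improvement, a log-rank test stratified by sites of about 8 patients gave 75% power against 81% unstratified in a simulation with hazard ratio 1.8 and no hospital differences, so the same step is not advised there.

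Stratifying does not repair the sample size. With 42 per arm, power for 80% against 90% is about 36% one-sided, and even at SD 2 the stratified test reaches only 46%. The stated 80% needs its own correction.

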### Concealment mechanism {16b}

Participants are randomized using an online randomization program, but the allocation concealment is not applicable as this is an open label trial.

### Implementation {16c}

All patients who give consent for participation and who fulfill the inclusion criteria will be randomized. Randomization will be requested by the investigator responsible for recruitment and clinical interviews. The clinical research associate and research nurse access the online program to randomization and then deliver the results to the investigator.

## Assignment of interventions: blinding

### Who will be blinded {17a}

Not applicable as this is an open label trial.

### Procedure for unblinding if needed {17b}

Not applicable as this is an open label trial.

## Data collection and management

### Plans for assessment and collection of outcomes {18a}

Data on demographic information, underlying disease, initial symptoms, diagnosis date, coronavirus Ct value, and laboratory and radiological findings is collected by the clinician. The clinician evaluates the seven-category ordinal scale of clinical status on admission, NEWS score and clinical course complications at hospitalization, treatment progress and clinical results, and side effects by drugs. Medical history is collected within 1 year before screening. In the case of single malignant tumors, medical history within 5 years before screening is collected. Information about underlying disease such as diabetes, hypertension, liver cirrhosis, chronic kidney disease without hemodialysis, end-stage renal disease, chronic heart failure, and lung diseases is collected regardless of period. At each visit, the National Cancer Institute Adverse Events Standard Terminology (NCI CTCAE) version 5.0 should be documented and recorded. The collection period for these reactions is from the start of treatment in the test or control group to day 28.

### Plans to promote participant retention and complete follow-up {18b}

#### Participants retention

Once a participant is enrolled or randomized, the researcher will make every reasonable effort to follow the participants for the entire study period. The research nurse will contact the participants before the scheduled follow-up date to avoid loss of follow-up.

